## Abstract

**Background:**

Short-term mindsets are associated with self-defeating behaviors, such as delinquency and alcohol use. In contrast, people who consider the longer-term consequences of their decisions tend to report positive outcomes, like feeling more competent and enhanced goal achievement. We evaluate an intervention, FutureU, that aims to stimulate future-oriented thinking, increase goal achievement, and reduce self-defeating behavior, by strengthening people’s identification with their future self. The intervention will be delivered through a smartphone application (app) or immersive Virtual Reality (VR). We test the effectiveness of FutureU for both delivery methods, examine working mechanisms, and identify potential moderators of intervention effects.

**Methods:**

In this Randomized Controlled Trial, a total of 240 first-year university students (*n* = 80 per condition) will be randomized into one of three conditions: (1) a smartphone condition, (2) a VR condition, and (3) an active control condition. We will assess proximal (i.e., future self-identification) and distal intervention outcomes (e.g., future orientation, self-defeating behaviors, goal achievement), user engagement, and examine usage data and goal content. Assessments will take place at baseline, during the intervention, immediately after the intervention, and at 3- and 6-months follow-up.

**Discussion:**

This study will provide information on the effectiveness of the intervention and allows for comparisons between delivery methods using novel technologies, a smartphone app versus immersive VR. Knowledge gained through this study can be used for further intervention development as well as theory building.

*Trial registration* This trial is registered on Clinicaltrials.gov (NCT05578755) on 13 October 2022.

## Background

Considering the future is an important aspect of psychosocial functioning. People who think ahead tend to make more balanced tradeoffs between the immediate and the long-term consequences of their choices [1, 2], and are more inclined to set goals they want to achieve in the future [3]. This results in positive outcomes such as feeling more competent, enhanced goal achievement, saving more, and having better educational records [e.g., 3–4]. In contrast, people who are more focused on the present are also more likely to act on impulse and prefer immediate rewards over larger, delayed rewards [1, 2]. Short-term mindsets are associated with self-defeating behaviors in various domains [e.g., 5]. In order to bolster positive development and goal attainment, and to diminish self-defeating behaviors, the FutureU intervention aims to stimulate future-oriented thinking by increasing future self-identification. The present study examines (1) the effectiveness of the FutureU intervention, (2) working mechanisms, and (3) moderators of intervention effects.

### Intervention theory

The degree to which people consider the future may be related to the degree to which they identify with who they will be in the future, i.e., their ‘future self’ [e.g., 6–10]. People who fail to identify with their future self may underweight or ignore the consequences of their decisions for this remote self [11], similar to how people tend to underweight or ignore the consequences of their decisions to others if left unimagined [12]. The level of identification with one’s future self is assumed to be determined by the extent to which people are able to vividly imagine (i.e., vividness), feel positively towards (i.e., valence), and feel similar and connected to their future self (i.e., related) (in the literature also referred to as ‘future self-continuity’, e.g., [6]). Strengthening the degree to which people identify with their future self may increase their tendency to make choices that favor the needs and wants of the future self over those of the present self [11]. In support of this assumption, empirical research shows that increasing the vividness of the future self is related to positive outcomes in different domains such as reduced delinquency [9, 10], increased exercise behavior [7], and higher savings [4]. Thus, future self-identification seems to positively affect psychosocial functioning.

Our perspective aligns with both identity-based motivation theory [13], and the self-activation hypothesis [14]. According to identity-based motivation theory, our identity functions as a motivator to work towards goals. That is, when people feel a psychological bond with their future self and have integrated an image of their future into their identity, they are more likely to undertake action and make decisions to become this future self and achieve their goals [13]. The self-activation hypothesis posits that behavior is guided by values incorporated into one’s identity. When values are cognitively activated, people will act in line with these values [14]. Hence, people may act according to the values associated with their image of the future when the cognitive representation of the future self is activated.

Our intervention aims to stimulate future-oriented thinking and future self-identification by: (1) actively encouraging participants to imagine their future and the goals they want to achieve in general, (2) explicitly inviting them to contemplate their future self, and (3) enabling them to interact with virtual renderings of their future, i.e., (digitally) aged, self. Vividness of the future and future self plays a particularly important role in our approach. A detailed and vivid image of the future creates the feeling that the future is likely to occur and is close in time, and render people more inclined to make future-oriented choices [15].

We combine this approach with a form of mental time travel commonly referred to as episodic future thinking, which refers to the ability to imagine or simulate *specific* events that may take place in one’s personal future [16, 17]. This has been applied in previous effective interventions addressing diverse behaviors such as impulsive eating [18], food purchases [19], and smoking [20]. For example, in one intervention participants had to vividly imagine and describe a potential future event, including where they were, what they were doing, who were with them, and how they felt. Subsequently, they recalled this event before undertaking a certain task [19]. The more vividly this potential future event was imagined, the larger the intervention effects appeared to be [18], again highlighting the importance of vividness in imagining the future (self).

### Smartphone application versus virtual reality

Given the important role of vividness in both increasing future self-identification and episodic future thinking, new technologies that allow for the transfer of visual information, such as smartphone applications (apps) and immersive Virtual Reality (VR), seem eminently suited as implementation tools. In contrast to traditional interventions, which rely heavily on people’s imaginative abilities [e.g., 19], apps and VR environments provide visual support. For example, age-progressed renderings of participants representing the future self can support people's ability to imagine it. This can reduce the intervention’s cognitive burden as well as the impact of individual differences related to people’s imaginative abilities on intervention effects [e.g., 21].

Both technologies also have unique features that could bolster intervention effects. Apps have few spatial or temporal restrictions: Participants can use them whenever and wherever they want to, including in the home environment [22]. A major advantage of implementing an intervention through an app, therefore, is the possibility of daily exposure to intervention content. To this end, preprogrammed push notifications can, for instance, remind participants to engage with the intervention, or deliver intervention-relevant messages, which, in turn, can increase participants’ treatment adherence [23]. Furthermore, apps create the opportunity to provide psychoeducation via multimedia tools, in which verbal communication can be combined with graphics, text and video, which results in improved recollection and treatment adherence [24].

Immersive VR, in contrast, allows for ‘virtual embodiment’ of the future self and facilitates perspective taking. Virtual embodiment refers to the substitution of an individual’s physical body by a virtual one, with the objective of generating the cognitive illusion that the virtual body is, at least temporarily, one’s own [25, 26]. This illusion of ownership over a virtual body can be induced when participants see their avatar from a first-person-perspective, for instance by seeing its reflection and synchronized movements reflected in a mirror [27]. Characteristics of the avatar that people embody can affect people’s attitudes, behaviors, and cognitions [27]. For example, Banakou et al. [27] found that participants embodying an avatar representing Einstein scored higher on a cognitive task and showed a decrease in age-based discrimination compared to participants embodying an ordinary adult avatar. Furthermore, VR facilitates perspective taking since participants can experience a situation from multiple perspectives, each time embodying a different avatar [25]. Within the FutureU intervention, this means that participants can literally take the perspective of their future self. Creating temporal and psychological distance from daily situations, in turn, can promote future-oriented choices [28].

### The present study

The current study has two aims. First, we aim to evaluate the FutureU intervention in a broad sense. We will assess the extent to which the intervention is able to stimulate future-oriented thinking, increase goal achievement, and reduce self-defeating behavior. More specifically, we will examine proximal intervention effects on outcomes related to future self-identification (i.e., vividness of, valence towards, and relatedness to the future self), and distal intervention effects on both primary (i.e., future orientation, consideration of future consequences, self-defeating behaviors, goal commitment, and goal achievement) and secondary (i.e., self-efficacy, academic results, and impulsiveness) outcomes. In addition, we will examine associations between usage patterns, user engagement, and intervention outcomes of both delivery methods, the FutureU smartphone application and the VR. We will additionally qualitatively analyze content (e.g., specificity, difficulty, and topic) of the goals that are set by participants during the intervention and examine them within the future self-identification framework. Furthermore, we will study whether intervention effects are mediated by increased future self-identification and explore potential moderators of intervention effects, such as personality traits (since personality traits have been linked to the use of new technologies; e.g., [29]). The second aim regards the exploration of differential intervention effects of the two implementation methods. Given that both technologies have their own unique features and advantages, we examine this aim exploratory.

Participants are first-year university students. Prior research suggests people are particularly susceptible to interventions during transformational life events and shifting contexts [14, 30]. During such events, they are more likely to take a ‘big-picture’ view of their lives, which can trigger behavioral changes [30]. Furthermore, a shift in surroundings influences the contextual information people receive, which can affect choices and decisions [14]. For most students, transitioning from secondary school to university is both a transformational life event and a change of context – moving to a new city, a new institution, living independently, being separated from family and close others – making this a relevant period to implement the FutureU intervention.

## Method

### Design

The current study regards an iteration and extension of a prior pilot RCT [see 31] evaluating the first version of the FutureU app. In the present study, the intervention will be examined through an RCT with three conditions: (1) a smartphone condition in which the intervention is implemented via (an iteration of) the FutureU app, (2) a VR condition in which the intervention is delivered through immersive VR, and (3) an active control condition in which participants set goals but receive no further intervention. Ethical approval was obtained from the independent Ethics Board of the Institute of Education and Child Studies at Leiden University (ECPW2021-320). The trial was registered on Clinicaltrials.gov (NCT05578755) on 13 October 2022.

In all conditions, participants start with an intake session. During this session participants give active informed consent, set personal goals, and complete an online questionnaire. In both intervention conditions, an avatar will be created and aged using a machine learning-based algorithm to generate a digital version representing their 10-year older, and hence ‘future’, self (see ‘Avatar Creation’ below).

All participants complete online questionnaires at baseline (i.e., during intake), at weekly intervals during the intervention (assessing a subset of the outcome variables), immediately after the intervention (i.e., three to four weeks after the intake), and at 3- and 6-months follow-up. For the smartphone condition, assessments occur on the 7th day of each of the three week-long modules (i.e., day 7, day 14, and day 21 of the intervention). For the VR condition, assessments occur at the start of the subsequent VR session about a week later. Additionally, future self-identification and the VR experience items are (also) assessed immediately after each VR session. For the control condition, assessments occur at time points parallel to those of the smartphone condition. Questionnaires not completed in time (i.e., within 4 days for the interim measurements, within 8 days for the post measurement, within 16 days for the 3-months follow-up, and within 32 days for the 6-months follow-up) will be treated as missing data.

After receiving participant’ consent, academic results will be requested from the university at the end of the academic year. Participants will receive €35,- or 8 course credits after completing all questionnaires up to the post-measurement. In addition, they will receive €20,- for completing both follow-up questionnaires (see Fig. 1 for the study flow chart).

**Fig. 1 Fig1:**
[figure not shown]
Study flow chart

### Avatar creation

Digital representations of participants, i.e., avatars, are created using various plug-in services and custom software developed specifically for the current purposes.^1^ To create the head of the present self-avatar of participants we use software developed by Avatar SDK, version ‘Head 2.0’ (www.avatarsdk.com). An age-progression service based on machine learning (www.changemyface.com) is then applied to create the future self-avatar.

We will use slightly different pipelines for avatar creation in the smartphone and the VR conditions. In the smartphone condition, the participant takes a ‘selfie’ during the intake using the integrated camera of the participant's smartphone. This image is age-progressed by approximately 10 years via a custom made server and the online service of Change My Face. The aged image is then converted into a 3D digital representation, to create the (avatar of) the future self.

In the VR condition, the (full body) avatar is created at the start of the first VR session in two stages. First, a webcam connected to the computer running the VR is used to make a photo of the participant’s face. For creating the avatar head, the remainder of the procedure is identical to the procedure in the smartphone condition. In the second stage, the body of the VR avatar is created using custom software developed for the research project. Through the use of several sliders, the experimenter adjusts the proportions of a generic male or female virtual body to match the proportions of the participant’s actual body and skin color. The colors of the present- and future self-avatars’ dress are made to differ to emphasize the difference the two.

### Participants and power calculation

We will include first-year students from a university in the Netherlands. Students with epilepsy will be excluded due to increased risk of seizures in VR. To determine sample size an a-priori power analysis was conducted with G*Power. We based our estimate of the effect size on a review of meta-analyses which showed that Cohen’s *d* effect sizes of universal interventions range from 0.23 to 0.58 [32]. Assuming a medium effect size of Cohen’s *d* = 0.40, a significance level of *p* < 0.05, three conditions, and one covariate, a sample size of 199 participants is estimated for a power of 80%. Based on a drop-out rate of 20%, we aim to include 240 participants, i.e., 80 participants per condition.

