### Recruitment and randomization

To recruit participants we will distribute flyers in university buildings and use communication channels of the university where the study is conducted, such as the university website and various social media channels. Additionally, we will ask student associations to distribute the advertisement of the study among their members.

Students interested in participating can schedule an appointment for the intake using an online portal. Before the intake, students are assessed for eligibility and randomly assigned to a condition on a 1:1:1 ratio using block randomization with blocks of 9, so that within a block three participants are allocated to each of the three conditions.

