##### Statistical analyses

The data will be analyzed using an intention-to-treat approach which implies that all randomized participants will be included in the analyses regardless of whether they actually completed the intervention or not. The three conditions will be compared on age and gender to examine potential differences at baseline. In case of baseline differences between the conditions, we will correct for them in the analytical models.

To test the effectiveness of the intervention and investigate differences in intervention effects between the two implementation methods, we will use regression models and ANCOVAs with the baseline measure of the concerned outcome as a covariate. Mediation will be examined with regression analyses. We will analyze whether the intervention conditions are associated with changes in the mediators (e.g., vividness, valence, and relatedness) and whether these changes, in turn, are related to changes in the intervention outcomes. Moderation of intervention effects will be analyzed with interaction effects in regression models and multigroup models.

Furthermore, we will study how (fluctuations in) usage patterns and engagement levels in an app and VR change over time and relate to intervention outcomes in an exploratory fashion using regression analyses possibly complemented with additional analyses (e.g., latent profile models). We will also qualitatively examine participants’ goal content, coding aspects such as the degree of specificity, the difficulty level, and the topic. Additionally, we will explore the role of goal content within the future self-identification framework. More specifically, we will relate aspects of goal content to the future self-identification scales (i.e., vividness, valence, and relatedness) over time, and examine the potential mediating role of self-efficacy in this context. Both will be analyzed with regression analyses.

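### The 199 participants quoted for 80% power match a one-degree-of-freedom, two-equal-group calculation, so the stated 80% is not supported for this three-arm trial

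*Protocol article*

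**What the plan says.** The sample size rests on one paragraph of the protocol article, Participants and power calculation. It says that "an a-priori power analysis was conducted with G*Power" and cites a review of meta-analyses in which "effect sizes of universal interventions range from 0.23 to 0.58". It then proceeds "Assuming a medium effect size of Cohen’s *d* = 0.40", with "a significance level of *p* < 0.05", and concludes: "three conditions, and one covariate, a sample size of 199 participants is estimated for a power of 80" per cent. The allowance for loss follows: "Based on a drop-out rate of 20%, we aim to include 240 participants, i.e., 80 participants per condition".

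Two other sections fix the layout that the power figure has to describe. Recruitment and randomization sets equal allocation to three arms, "using block randomization with blocks of 9, so that within a block three participants are allocated to each of the three conditions". Statistical analyses plans regression models and "ANCOVAs with the baseline measure of the concerned outcome as a covariate". The Abstract says effectiveness will be tested for both delivery methods, so each intervention arm has to be set against control. No section names a pooled comparison of both interventions with control.

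The power paragraph does not print the f value, the numerator degrees of freedom, the contrast that is powered or a baseline-outcome correlation.

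**The concern.** The paragraph lists three conditions among its inputs, but 199 is what the calculation returns when the effect has one numerator degree of freedom and f is half of d. Half of d is the right f only when the whole sample is divided into two equal groups. In a 1:1:1 trial, one intervention against control uses two thirds of the participants, pooling the interventions gives a 2:1 split, and an overall test of the arms has two numerator df. None of these is the layout behind 199.

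This is the only justification given for the sample size. A null result for the app or for VR would be read as coming from a test with a 20% chance of missing d = 0.40. If that d is already adjusted for baseline, the chance of missing it is nearly 40%.

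**Working it through.** **Inputs.** From Participants and power calculation: d = 0.40, alpha 0.05 (taken as two-sided, as an F test implies), three groups, one covariate, 80% power, N = 199, 240 randomised, 20% loss. From Recruitment and randomization: 1:1:1 allocation. Evaluable after loss: 240 × 0.80 = 192, or 64 per arm. The baseline-outcome correlation r is not given and is varied in step 4.

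**1. Reproducing 199.** Power = P(F′ > F crit), where F′ is noncentral F with λ = f²N and df2 = N − 3 − 1, and f = d/2 = 0.20.
- Numerator df 1, N = 199: λ = 0.04 × 199 = 7.96, df2 = 195, critical F = 3.890, power 0.802. At N = 198 power is 0.7996, so 199 is the smallest N.
- Numerator df 2, N = 199: critical F = 3.042, power 0.708. Power first reaches 80% at N = 244 (0.8002; 0.798 at 243).
- With numerator df 1, setting two or three groups and zero or one covariate all return 199. The match therefore identifies f and the numerator df, not the number of groups.
- Other f values tried do not give 199: f = 0.25 gives 158 (df 2) or 128 (df 1), and f = 0.40 gives 64 or 52.

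**2. Which layout this describes.** For two groups with shares p and 1 − p, f = d√(p(1 − p)), which equals d/2 only at p = 1/2. At N = 199:
- two equal groups using everyone: λ = 0.16 × 1/4 × 199 = 7.96
- one arm against another, using 2/3 of N: λ = 0.16 × 1/4 × 132.7 = 5.31
- both interventions against control, 2:1: λ = 0.16 × 2/9 × 199 = 7.08

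**3. Power at d = 0.40 with no credit for the covariate.** Contrasts use noncentral t with N − 4 residual df; the omnibus test uses noncentral F with 2 and N − 4 df.

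| Comparison | N = 199 | N = 192 | N = 240 |
|---|---|---|---|
| Each intervention vs control | 63% | 61% | 71% |
| Both interventions pooled vs control | 75% | 74% | 83% |
| Omnibus, f = 0.20 | 71% | 69% | 79% |
| Omnibus, both interventions 0.40 from control (f = 0.189) | 65% | 64% | 74% |
| Omnibus, three means evenly spaced over 0.40 (f = 0.163) | 52% | 51% | 61% |

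The last two rows apply only if 0.40 is the largest pairwise difference: f = 0.40 × √2/3 = 0.189 and f = 0.40/√6 = 0.163.

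Analysed totals needed for 80%: 297 for each intervention against control (99 per arm), 225 for the pooled contrast, and 244 for the omnibus test at f = 0.20. At 64 per arm, the smallest d detectable with 80% power for each intervention against control is 0.50.

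**4. If d = 0.40 is on the unadjusted scale.** Baseline adjustment then gives an effective d of 0.40/√(1 − r²). Each intervention against control at 192:
- r = 0.3: d = 0.419, power 66%
- r = 0.5: d = 0.462, power 74%
- r = 0.6: d = 0.500, power 80%

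For this contrast the crossing to 80% is at r of about 0.60 with 192 analysed, 0.58 with 199 and 0.44 with 240. The pooled contrast crosses at about 0.37 with 192 and 0.33 with 199.

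**The case against.** The strongest reply is that the planned analysis adjusts for baseline and the effect sizes are quoted simply as Cohen's d, so d = 0.40 may be unadjusted and the real power higher than step 3 shows. This stands as far as it goes: at r of about 0.6, each intervention against control has 80% power with 192 analysed. It does not rescue the printed figure, because the protocol gives no correlation. In the ANCOVA calculation that returns 199, f enters as an already adjusted effect and the covariate costs only a degree of freedom.

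Second, the analysis is by intention to treat with all randomised participants, so 240 might be the relevant total. The Design section treats late questionnaires as missing, and the power paragraph itself expects 20% loss, so 240 is an upper bound. Even there, each intervention against control has 71%.

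Third, the numerator df is inferred. That is true, but the match is exact and none of the other settings tried returns 199.

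A reader might go further and infer that no comparison in this trial can reach 80% power. The documents do not support that. The pooled contrast has 83% if all 240 are analysed, and a moderate or high baseline correlation lifts the others. Nor is 61–63% an established fact about the trial: it holds if d = 0.40 is already adjusted or r is zero. The omnibus figures near 51% need the further assumption that 0.40 is the largest difference and that the means are evenly spaced, which the protocol does not say.

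An analysis plan that is not shown may name the contrasts. Leaving that detail out of an article is not the fault here; the fault is a printed N and power that do not fit the printed three conditions.

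**Conclusion.** The concern holds in this form: 199 is not the number that gives 80% power at d = 0.40 for three conditions. It matches a 1-df test on two equal groups, and the 2-df test at the same f needs 244. On the stated inputs at 199 / 192 evaluable, power is 63% / 61% for each intervention against control, 75% / 74% pooled, and at most 71% / 69% for the omnibus test.

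These figures assume two-sided alpha 0.05, equal arms and a d of 0.40 that already reflects baseline adjustment. If d is unadjusted, power for each intervention against control at 192 is 66% to 80% over r = 0.3 to 0.6. The claim of 80% is therefore unsupported as written, rather than shown to be unattainable. Effect estimates and the type I error rate are not affected.

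**What to change.** Keep 240 and replace the power statement in Participants and power calculation with one for each intervention against control. Either form would do:
- *With 192 evaluable participants (64 per arm), each comparison of an intervention with control has 61% power for a covariate-adjusted d = 0.40 at two-sided alpha 0.05; the smallest such d detectable with 80% power is 0.50.*
- State that d = 0.40 is unadjusted, give the assumed baseline-outcome correlation with its basis, and quote the power at that value: 66% at r = 0.3, 74% at 0.5, 80% at 0.6.

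Either version should print the f or d used and the numerator df, so that the figure can be reproduced. The pooled comparison need not become the lead contrast; that would be a design choice, and this correction does not depend on it. The cost is one reworded paragraph and, unless a high correlation can be justified, a less favourable power figure. Recruitment, conduct and analysis stay as planned.

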## Discussion

The present study tests a novel intervention, FutureU, which aims to stimulate future-oriented thinking, increase goal achievement and reduce self-defeating behavior by strengthening people’s future self-identification. We will evaluate FutureU by examining its effectiveness, its working mechanisms, and potential moderators of intervention effects. Additionally, we will explore usage patterns, engagement levels, and goal content within an intervention context. The intervention will be delivered through an app and immersive VR. Both technologies have their own advantages for intervention implementation, though they are rarely simultaneously included in research designs. Our three-arm RCT provides a unique opportunity to compare these two technologies as implementation strategies.

Although the use of technology for intervention implementation is appealing, it also comes with challenges. First, if people consider the app or VR as unappealing, they may stop using it or feel less engaged [23]. In order to make the app and VR environment attractive and engaging we conducted extensive user-tests, using questionnaires as well as qualitative interviews, and a large-scaled pilot RCT examining an earlier version of the FutureU app intervention [31] in which we collected data regarding user experiences, app use, and intervention effects. Earlier versions of the virtual environment have been used in prior research as well [10]. Based on feedback on prior iterations, we iterated both the app and the VR. In the current RCT, we will collect usage data to examine to what extent treatment adherence (e.g., using the app each day, participating in all VR sessions) is a concern. Second, drop-out rates tend to be relatively high in studies using new technologies [23]. In addition, our study includes multiple measurement points which, although strengthening our study design, also increases participant burden. Therefore, besides the substantial effort we have put into the development of an engaging intervention, participants also receive compensation (financially or with course credits) for their participation.

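### The 199 participants for 80% power come from a two-equal-group, one-degree-of-freedom calculation in which the covariate has no effect, so 80% is not the power of the planned baseline-adjusted three-arm analysis

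*Protocol article*

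**What the plan says.** Under Participants and power calculation, the article says that "an a-priori power analysis was conducted with G*Power". The effect size rests on a review of meta-analyses whose "effect sizes of universal interventions range from 0.23 to 0.58", and the text continues: "Assuming a medium effect size of Cohen’s *d* = 0.40". The remaining inputs are a 0.05 significance level and the design, and the result follows in the same sentence: "three conditions, and one covariate, a sample size of 199 participants is estimated for a power of 80" percent. Enrolment is then set at 240, or 80 per condition, for 20% drop-out.

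Under Statistical analyses, effectiveness and the comparison of the two delivery methods are to be tested with "regression models and ANCOVAs with the baseline measure of the concerned outcome as a covariate".

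Table 2 shows a baseline (T1) assessment for most outcomes. It shows none for weekly goal achievement, monthly goal achievement or academic results. The two goal-achievement measures are listed among the primary distal outcomes.

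The power paragraph does not say on which standard-deviation scale d is expressed, gives no baseline-outcome correlation, and does not name the contrast that was powered.

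**The concern.** The calculation is presented as one for three conditions with a covariate, which sounds like the planned analysis. Two features suggest that it is not.

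- **Covariate.** In an ANCOVA power calculation, f is relative to the residual standard deviation after adjustment, SD × √(1 − r²). A raw-SD d entered as f = d/2 amounts to r = 0. The covariate then only uses up one error degree of freedom. This understates power wherever r is not 0.
- **Contrast.** Converting d to f by halving it is right for two equal groups. The trial has three equal arms, and every contrast among them carries less information than a half-and-half split of the same total. This overstates power.

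The two features pull in opposite directions, so the quoted 80% may be too high or too low, depending on the contrast and on r. The figure matters because readers will use it to decide how much a null result means.

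**Working it through.** **Inputs from the article:** d = 0.40; alpha 0.05 (taken as a two-sided or F test); 3 groups; 1 covariate; N = 199; 1:1:1 allocation; 80 per arm; 20% drop-out. **Assumed:** d in raw SD units, and r from 0 to 0.7.

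**Step 1. Reproduce 199.** Noncentral F with λ = N·f² and error df = N − groups − covariates.

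- f = 0.40/2 = 0.20, numerator df 1, 3 groups, 1 covariate: power is 79.96% at N = 198 and 80.2% at N = 199. The answer is 199, an exact match.
- The same with no covariate: 199. The same with two groups instead of three: 199.
- Numerator df 2 (overall three-group test) at f = 0.20: N = 244, and power at 199 is 70.8%.
- Numerator df 2 with both interventions differing from control by d, f = 0.40 × √2/3 = 0.1886: N = 275, and power at 199 is 65.3%.

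Of the variants tried, only f = 0.20 with one numerator df gives 199.

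**Step 2. Which comparison does that noncentrality belong to?** λ = 199 × 0.20² = 7.96, which equals N·d²/4 = 199 × 0.16/4, the value for two equal groups of N/2. With three equal arms of n = N/3 and r = 0:

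- One arm versus control: λ = n·d²/2 = N·d²/6 = 199 × 0.16/6 = 5.31, power 63%.
- Both arms pooled versus control: λ = n·d²/1.5 = N·d²/4.5 = 199 × 0.16/4.5 = 7.08, power 75%.

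Neither reaches 7.96.

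**Step 3. Add the covariate and the expected completers.** Completers are 80 × 0.80 = 64 per arm, 192 in total, so error df = 192 − 3 − 1 = 188. Adjustment divides λ by (1 − r²). At r = 0, λ is 64 × 0.16/2 = 5.12 for a pair and 64 × 0.16/1.5 = 6.83 for pooled versus control.

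| r (assumed) | 1 − r² | λ, one arm vs control | Power | λ, pooled vs control | Power |
|---|---|---|---|---|---|
| 0 | 1.00 | 5.12 | 62% | 6.83 | 74% |
| 0.3 | 0.91 | 5.63 | 66% | 7.50 | 78% |
| 0.5 | 0.75 | 6.83 | 74% | 9.10 | 85% |
| 0.6 | 0.64 | 8.00 | 80% | 10.67 | 90% |
| 0.7 | 0.51 | 10.04 | 88% | 13.39 | 95% |

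At 64 per arm, 80% is reached at r of about 0.60 for one arm versus control and about 0.37 for pooled versus control.

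**Step 4. Outcomes with no baseline measure.** For weekly and monthly goal achievement and academic results there is no baseline of the outcome to adjust for, so the r = 0 row applies: about 62% and 74%.

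**The case against.** **The stated inputs give the stated output, and r = 0 is a legitimate conservative choice.** Both parts are true. Taken alone, ignoring the gain from baseline adjustment can only understate power. This part of the point does not show that the trial is too small. It does not rescue the 80%, however, because the two-group noncentrality errs the other way.

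**The raw-SD scale of d and the value of r are not in the document.** This also stands. A reader might infer that the 80% is wrong for every outcome with a baseline measure. The article does not support that. It depends on d being a raw-SD effect and on r differing from 0, and r may vary by outcome and by follow-up time (three to four weeks, 3 months, 6 months). If d was meant on the adjusted scale, saying so would settle the covariate part and leave the contrast part.

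**A smaller trial would do.** A reader might re-run the 199 calculation with f divided by √(1 − r²), obtain 181, 150, 128 or 103 at r = 0.3, 0.5, 0.6 or 0.7, and take these as the sample sizes needed. They are not. They keep the two-equal-group noncentrality, so they give 80% power for no contrast among three equal arms.

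**A journal article condenses, and r could be in a fuller document.** This would excuse silence. Here the article states the inputs and the result, and that result can be checked against the analysis that the same article describes.

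**Conclusion.** The point holds in a limited form. The 199 for 80% is a two-equal-group, one-degree-of-freedom result on which the covariate has no numerical effect. It is not the power of the baseline-adjusted three-arm analysis. At 64 completers per arm and d = 0.40, power runs from about 62% to 88% for one arm versus control and from about 74% to 95% for pooled versus control, as r goes from 0 to 0.7.

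These figures assume that d is in raw SD units, that drop-out is 20% in each arm, that tests are two-sided at 0.05 without multiplicity adjustment, and that these are the contrasts intended.

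A reader might infer that the trial is under-powered. The documents do not establish that: it depends on r and on the contrast, and the article gives neither. What they do establish is that one 80% figure cannot stand for all the comparisons and outcomes.

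**What to change.** In Participants and power calculation:

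1. Say whether d = 0.40 is in raw or covariate-adjusted SD units.
2. State the assumed baseline-outcome correlation, by outcome where possible. The cited pilot RCT, "in which we collected data regarding user experiences, app use, and intervention effects", is a natural source. If it cannot supply r, show the range 0 to 0.7.
3. Replace the single 80% with the power of each planned contrast, named as such, at the expected 64 completers per arm. The table above can be used if the assumptions are accepted.
4. Give the r = 0 figures separately for weekly and monthly goal achievement and academic results.

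The cost is a few sentences or a small table and a re-run of the calculation. Enrolment stays at 240 and nothing in the conduct of the trial changes.
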